## Abstract

**Background:**

Gait disorders in individuals with Parkinson’s disease (PD) may be associated with alterations in the motor control system and aggravated by psychoemotional and cognitive issues. Therapeutic strategies aimed at self-perception and motor regulation seem to be promising. Motor imagery (MI) has been shown to be one of these strategies, but there is still no clear evidence of its applicability in this population. The aim of this trial is to determine the effects of motor-imagery training on the gait and electroencephalographic activity of individuals with PD.

**Methods/design:**

The sample will consist of 40 individuals, aged between 45 and 75 years, in the mild and moderate phase of the disease, with the ability to generate voluntary mental images. They will be assessed for cognitive level, degree of physical disability, mental-image clarity, kinematic gait variables, electroencephalographic activity and mobility. Next, subjects will be randomly assigned to an experimental group (EG) and a control group (CG). The EG will perform motor imagery and gait, while the CG will only engage in gait exercises. Twelve training sessions will be conducted lasting up to 90 min each, three times a week, for 4 weeks. The subjects will be reassessed on the kinematic variables of gait, electroencephalographic activity and mobility at 1, 7 and 30 days after the final training session.

**Discussion:**

The results may provide an important advance in neurological rehabilitation where an easy-access and low-cost intervention may help to improve gait, electroencephalographic activity and mobility in individuals with PD.

**Trial registration:**

Clinicaltrials.gov, ID: NCT03439800. Registered on 15 November 2017.

**Electronic supplementary material:**

The online version of this article (10.1186/s13063-019-3694-8) contains supplementary material, which is available to authorized users.

## Background

Motor alterations caused by Parkinson’s disease (PD) significantly affect gait, creating cognitive dependence in improving movement patterns; that is, gait becomes more vulnerable to external influences [1]. External clues provide information and require the individual’s attention to movement, activating frontal cortex regions to control its execution [2–4]. Studies suggest that these clues may help improve gait pattern and electroencephalographic (EEG) activity in patients with PD [5, 6]. A recent review study conducted by Bočková and Rektor (2019) [7] indicates that patients with PD face a general slowdown of background activity, excessive synchronization of beta-rhythm activity and disturbed movement-related gamma-rhythm oscillations in the basal ganglia and in the cortico-subcortical and cortico-cortical motor loops, suppressible by dopaminergic medication, as well as by high-frequency deep-brain stimulation. Although dopaminergic therapy is currently the best treatment for PD, gait dysfunctions are commonly resistant to drug therapy, especially in the advanced stages of the disease.

Motor imagery (MI) [8], defined as imagining a motor action without physically executing it [9], is a cognitive strategy that, along with other types of external clues, demands attention to the sequence of a trained movement, which can be performed visually or kinesthetically. It has been shown that MI can produce replicable EEG patterns over primary sensory and motor areas [10, 11], and despite deficits in the supplementary motor area from the indirect effect of the basal ganglia, patients with PD have preserved locomotor imagery observed during the on-medication state [12]. The mesencephalic locomotor region (MLR), located in the brainstem region and consisting of the pedunculopontine and cuneiform nuclei, is modulated by changes in imagined locomotion in healthy humans [13]. MLR also modulates cortical networks similar to those involved during real gait [14].

In neurological rehabilitation, the use of MI has generally been associated with physical practice (PP). Motor imagery has several advantages, such as the opportunity to increase the number of repetitions safely and autonomously, without excessive fatigue, in addition to allowing the mental training of motor tasks, when and where the patient wants or is able to perform them. Furthermore, MI enables more demanding or complex motor tasks, such as gait, or when PP is impossible or very difficult. Despite these advantages, MI is a complex process that is not easy to integrate into clinical practice [15]. Its association with PP, however, seems to be more effective than PP alone in enhancing motor function [16].

Two studies that associated MI with PP, in order to determine the motor effects on individuals with PD, showed a significant decline in bradykinesis [17] and an improvement in the kinematic aspects of gait [18]. Another study that correlated MI with PP showed no gait improvement in individuals with PD [19]. A fourth study that compared MI with relaxation sessions, both associated with PP, found no improvement in the mobility of these patients [20]. The protocols used, different training times between studies and the lack of follow-up precluded confirming the duration of the effects observed.

In light of the gaps in the methodologies presented, a therapeutic plan can be devised involving MI, which has been shown to be promising, albeit still inconclusive. As such, there is a need to develop more effective training protocols in order to optimize the rehabilitation process of individuals with PD. To that end, a new MI protocol associated with gait was created for patients with PD, based on the protocols of El-Whishy [18] and Santiago [19], but differing in terms of training time, observation method and follow-up.

Few PD studies have investigated EEG functions during gait activity. Therefore, this study aims to contribute to the literature on the pattern of brain activation (coherence intra- and inter-hemispheres and the spectral power of alpha and beta rhythms) of individuals with PD during gait activity, before and after the MI intervention. Clinical quantitative measures of gait and mobility, most commonly investigated by other studies, will also be analyzed and correlated with EEG data.

Thus, this randomized clinical trial protocol should determine the effects of MI training on the gait and EEG activity of individuals with PD.

## Methods/design

### Design

This is a single-blind, randomized controlled clinical trial, in line with the Standard Protocol Items: Recommendations for Interventional Trials (SPIRIT) guidelines (Fig. 1). It will be conducted at the Laboratory of Intervention and Analysis of Movement (LIAM), in the Physical Therapy Department of the Federal University of Rio Grande do Norte (UFRN). Participants will be recruited from a population of patients with PD treated in public and private hospitals and reference centers in the city of Natal, Rio Grande do Norte state, Brazil. They will be randomly allocated to an experimental group (EG; MI associated with PP) or a control group (CG) (only PP). Outcome measures will be collected by trained researchers at the start (week 0) and at the end of the intervention (weeks 5 and 6), and 1 month after the intervention (week 10). Analyses of inclusion criteria, obtaining informed consent, data collection and statistical analyses will be carried out by the researchers, who will be blind to group allocation. Participants will be evaluated and advised of the study procedures, in addition to giving their informed consent. This project was approved by the Research Ethics Committee of the Federal University of Rio Grande do Norte, under protocol number 2.057.658 and registered as a clinical trial at www.ClinicalTrials.gov (ID: NCT03439800).

**Fig. 1 Fig1:**
[figure not shown]
The schedule of enrollment, interventions and assessments demonstrated in the Standard Protocol Items: Recommendations for Interventional Trials (SPIRIT) Figure

### Sample size estimates

The sample size was calculated using the OpenEpi public domain program, version 3.01 [21]. The calculation, based on the outcome variable “hip range of motion” of individuals with PD submitted to MI associated with the PP of gait, obtained by El-Whishy et al. [18] A power of 80% was considered as well as a 95% confidence interval. The mean and standard deviations were 54.7° and 7.2°, respectively, from which the sample size of 34 individuals (17 in each group) was obtained. Added to this value was 10% for possible sample losses, resulting in a final sample of 40 individuals, 20 each in the two groups under study.

### Participants

#### Inclusion and exclusion criteria

Patients will be included according to the following criteria: (1) Diagnosis of PD by a neurologist; (2) Age between 45 and 75 years; (3) In the mild to moderate phase of the disease (including patients between stages 1.5 and 3 on the Hoehn and Yahr scale) [22]; (4) Using antiparkinson medication, without adaptation during study participation; (5) Exhibiting no cognitive impairment, according to the Mini-Mental State Examination (MMSE). The cutoff point was established considering the individuals’ schooling (illiterate: 18; some schooling: 24) [23]; (6) Be able to imagine motor activities in the kinesthetic modality (according to the Revised Movement Imagery Questionnaire – MIQ-R). The cutoff point was 20 for the kinesthetic modality, indicating at least “somewhat easy to feel” the kinesthetically imagined movement [24]; (7) Not having undergone stereotaxic surgery; and (8) No other associated neurological diseases; no musculoskeletal alterations that hinder gait; corrected vision or hearing. The following patients will be excluded: (1) Those exhibiting hemodynamic instability before or during training (systolic and diastolic blood pressure above 180 mmHg and 110 mmHg, respectively) [25]; (2) Not understanding any stage of the training protocol; and (3) Experiencing acute pain and/or discomfort that would hinder the proposed activities.

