### Randomization

Randomization will be computer-generated in randomized blocks using the randomization.com system. The process will be carried out by a volunteer not affiliated with the research, who will preserve allocation anonymity, randomly separating the individuals into a control group (CG) and experimental group (EG). The volunteer will also prepare sealed envelopes, using codes to represent the groups.

Only the researchers in charge of conducting the training sessions will be aware of meaning of each code and participant allocation. They will open the envelope corresponding to the patient number before patients start the training.

The researchers responsible for the initial assessment and reassessment will not be informed of allocation during data collection and statistical analysis. Data analysis will also be performed by one of the evaluators, who will only have access to the codification and will not be informed about which group each code corresponds to.

The present protocol has been prepared in accordance with relevant items from the SPIRIT Checklist (see Additional file 1) and the SPIRIT Figure (Fig. 1).

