### Intervention

This protocol will be based on those of El-Whishy [18] and Santiago [19]. Training will start on the day following the initial assessment, which will be divided into 2 days.

The subjects who are randomly allocated to the EG will be submitted to a protocol consisting of five training stages, as follows: awareness, problem identification, progressive relaxation, MI of the task and PP of the task. The CG will undergo the following stages: awareness, problem explanation, progressive relaxation and PP of the task; that is, stages 1, 2, 3 and 5.

After opening the identification envelope, the researcher in charge of training will describe the stages that the participants will be submitted to. Before this, blood pressure and heart rate will be measured and monitored by a digital sphygmomanometer (Visomat Comfort III, Incoterm*®,* São Paulo, Brazil).

In the event that patients exhibit altered vital signs, they will be asked to remain seated and try to relax. If the situation persists, the patient will be instructed to visit their physician.

Before training sessions begin, the researcher in charge will ask the patient to walk around the course to be used that day if it is the first, fifth or ninth session, so that the execution time can be recorded and used during the fourth stage. A detailed description of the training protocol is shown below.

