### Data analysis

Data analysis will be conducted with the following variables: (1) Kinematic: speed (m/s), stride length (m), stance and swing time (s) of the most affected limb, hip range of motion, maximum hip extension during stance (°), maximum hip flexion during swing (°), maximum knee flexion during swing (°) and ankle dorsiflexion (°); (2) EEG activity: alpha (8–12 Hz)- and beta (13–30 Hz)-frequency bands; and (3) Mobility: average time to conduct the TUG.

Analysis of variance with repeated measures will be used to determine whether there are statistically significant differences between baseline, post training and monitoring measures of the CG and the EG.

Group descriptions will be presented as means and standard deviations. Intention-to-treat analysis will be conducted for dropout data, using the last available value to represent the absent assessment sessions.

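### The comprehension exclusion can be judged only after allocation and has more scope in the imagery arm; the protocol does not say that randomised patients who meet it stay in the intention-to-treat analysis

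*Protocol article*

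**What the plan says.** All of this is in the protocol article.

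- **Inclusion and exclusion criteria.** Three exclusions are listed: (1) "Those exhibiting hemodynamic instability before or during training", (2) "Not understanding any stage of the training protocol" and (3) "Experiencing acute pain and/or discomfort that would hinder the proposed activities". The first covers time before and during training, the second gives no time point but refers to the training stages, and the third gives no time point.
- **Abstract (Methods/design).** Random assignment follows the baseline assessment.
- **Randomization.** Only the trainers know what the codes mean: "They will open the envelope corresponding to the patient number before patients start the training".
- **Intervention.** The trainer describes the stages after opening the envelope. For the experimental arm: "The subjects who are randomly allocated to the EG will be submitted to a protocol consisting of five training stages". The CG has four of these and omits imagery.
- **Data analysis.** "Intention-to-treat analysis will be conducted for dropout data", with the last available value standing in for missed assessments. The Discussion lists intention-to-treat among the study's strengths.

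**The concern.** An eligibility rule protects a randomised comparison only if it is applied before allocation is known. Criterion 2 depends on the patient's response to stages that are explained once the arm is known, to staff who know it, and the stages differ between arms. If meeting the criterion means leaving the trial, the two groups analysed are no longer the two groups randomised, and the selection can differ by arm. With 20 patients per arm, a few exclusions on one side can move the result, and a larger sample would not remove such a bias. The intention-to-treat statement would normally answer this, but the article applies it to dropout data and does not say whether a patient excluded during training counts as a dropout.

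**Working it through.** **1. Order of events.** Baseline assessment over two days → randomisation → trainer opens the envelope → trainer describes that arm's stages → 12 sessions → assessments at 1, 7 and 30 days. No comprehension check of the stages is described before the envelope is opened. Criterion 2 therefore acts after allocation, criterion 1 on either side of it, and criterion 3 possibly on either side.

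**2. Scope by arm.** EG: awareness (comparing one's own gait video with normal gait), problem identification, relaxation, imagery, physical practice (5 stages). CG: a general video on Parkinson's disease, explaining that video, relaxation, physical practice (4 stages). Imagery exists only in EG, and the first two stages differ in content. There are more ways to meet criterion 2 in EG.

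**3. Who judges.** The Design section gives the analysis of inclusion criteria to researchers blind to allocation. Understanding of the stages is seen by the trainers, who are not blind.

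**4. The plan's own figure.** The article gives SD 7.2°, 80% power, 95% confidence and 17 per arm, but no difference. Solving backwards (two-sided 0.05 assumed): 7.2 × (1.960 + 0.842) × √(2/17) = 6.92°. The 17 per arm cannot be reproduced independently, so 6.92° serves only as a yardstick. At 6.92°, power is 86% with 20/20 patients, 83% with 17/20 and 82% with 16/20. Lost power is not the main harm.

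**5. Possible shift, by formula.** If k of 20 EG patients are removed and they average D below those who remain, the EG mean rises by k × D / 20. D is an assumption. For D = 7.2° (1 SD): k = 2 gives 0.72°, k = 3 gives 1.08°. For D = 0 the shift is 0, and for D = -7.2° it is -0.72° and -1.08°. For change from baseline, D is replaced by D(post) - D(baseline). A deficit that is equally large at baseline cancels.

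**6. Possible shift, by simulation.** No true effect, 20 per arm, SD 7.2°, 40,000 replicates, t-test on final values. The k EG patients with the lowest comprehension score are removed and none from CG. ρ, the score's correlation with hip range of motion, is an assumption.

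| ρ | shift, k = 2 | type I error, k = 2 | shift, k = 4 | type I error, k = 4 |
|---|---|---|---|---|
| -0.3 | -0.38° | 0.053 | -0.72° | 0.060 |
| 0 | 0 | 0.049 | 0 | 0.052 |
| 0.3 | +0.40° | 0.054 | +0.72° | 0.059 |
| 0.5 | +0.65° | 0.062 | +1.21° | 0.080 |
| 1 (extreme) | +1.30° | 0.099 | +2.40° | 0.198 |

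With 3 removed from EG and 2 from CG, the shift runs from -0.17° to +0.53°. With 2 removed from each arm it is about 0.

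**7. If excluded patients are kept by carrying the last value forward.** A patient stopped before the first reassessment carries baseline forward and shows zero change. The EG mean change is then multiplied by (20 - k)/20, which is 0.90 for k = 2. If training improves gait, this shrinks the EG change, the opposite direction to most of the table.

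**The case against.** The strongest reply is that the article never says excluded patients leave the analysis. Every randomised patient has a baseline value, so if exclusion means only that training stops, the last-value rule can satisfy intention-to-treat as written. This stands: the conflict is conditional. But the article does not state that reading, and the ordinary meaning of an exclusion criterion is that the patient is not in the trial.

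Second, all patients must reach the kinesthetic imagery cutoff on the MIQ-R and the MMSE cutoff for their schooling. EG patients may receive hints and encouragement, and CG patients also have to explain what they watched. This stands too and should limit both the number of failures and the imbalance. Neither instrument tests understanding of this protocol's stages, however.

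Third, the Design section says patients are advised of the study procedures around consent, so a gross failure to understand might show then. That is possible, but the stage descriptions come after the envelope.

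A reader might also infer three stronger points that the article does not support:

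- **That all these rules act only after randomisation.** Criterion 1 expressly covers the time before training, and criterion 3 has no timing. The medication requirement, "Using antiparkinson medication, without adaptation during study participation", is an inclusion criterion, and nothing says that a later change removes anyone.
- **That bias towards motor imagery is established.** Its direction depends on how those excluded would have fared and on the imbalance in exclusions. The article gives neither.
- **That the bias is a definite share of the planned difference.** Any such share needs an unsourced deficit, such as 1 SD, and a stable deficit largely cancels in the planned repeated-measures comparison with baseline.

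**Conclusion.** The concern holds in a limited form. Criterion 2 operates after allocation as the procedures are written, is observed by unblinded trainers, and has more scope in EG. Criterion 1, and possibly criterion 3, can also act after allocation. If such patients are removed from the trial, this conflicts with the stated intention-to-treat analysis and can bias the comparison.

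The size is unknown. Under the assumptions above, removing 2 of 20 from EG alone shifts the difference by -0.38° to +1.30°, and near-equal removal shifts it by much less. A shift favouring EG is plausible if those excluded would have done worse. This rests on three assumptions: criterion 2 means failing on any one stage, removal from the trial is what exclusion means, and final values are compared. It should be fixed, but it does not invalidate the design.

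**What to change.** 1. During the two-day initial assessment, before the envelope is opened, describe the stages of both arms to every patient, check understanding, and apply criterion 2 there.
2. Add a sentence along these lines: a randomised patient who later meets any exclusion criterion stays in the trial, is invited to the 1-, 7- and 30-day assessments, and is analysed in the allocated group. Report the number and reason by arm.
3. The eligibility section excludes for haemodynamic instability before or during training. The Intervention section has patients with altered vital signs rest and, if the problem persists, see their physician, without mentioning exclusion. The investigators must reconcile these passages; no clinical rule is proposed here.

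The cost is a change of wording and a short check within visits already planned. The downside is slight dilution of the effect by patients who stop training but stay in the analysis.

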### Outcomes

#### Primary outcome

The hip range of motion, a kinematic variable of gait, will be obtained by the Qualisys Motion Capture System (Qualisys Medical AB, 411 13, Gothenburg, Sweden). This system records the spatio-temporal variables of gait, as well as the angular variations of the hip, knee and ankle joints. It is a photographic system based on a video that reconstructs movement in three dimensions (3D), composed of six Qualisys Oqus 300 cameras, connected in series and that emit and capture infrared light, which is reflected by spherical markers placed on specific anatomical structures.

#### Secondary outcomes

The secondary outcomes will be the spectral power of the alpha and beta rhythms, intra- and inter-hemisphere coherence between frontal and fronto-central channels and mobility. Electroencephalographic activity will be measured by Emotiv EPOC+, which provides EEG data. The device uses contact sensors attached to the flexible plastic arms of a wireless headset. The headset has 14 sensors that are able to detect facial expressions, head rotation, emotions and conscious mental commands. For the present study, the changes in EEG activity captured on the surface of the patient’s head will be monitored before and after 12 training sessions (including follow-ups). MATLAB software will be used to process the data [26, 27]. Mobility will be assessed by the Timed Up and Go Test (TUG). This consists of rising from an ordinary chair (with no arms), walking 3 m, turning through 180°, and sitting down again as fast as possible wearing typical walking shoes. The shorter the time to perform the activity, the better the mobility [28]. The time spent on the two attempts will be recorded using a digital stopwatch.

